### Instruments

The evaluations will be performed at screening, baseline, post-treatment, and 6- and 12-month follow-ups. All variables and assessment periods of the study can be found in Table 1. Scores on depression, negative and positive affect, and opinions about the modules will also be obtained after each completed module in the face-to-face and Interned-based MBIs. Participants in the TAU group will report their general opinion about the treatment as usual received at the end of the program.

**Table 1 Tab1:** Study outcomes

Instruments	Assessment Area	Time of assessment^a^
Sociodemographic	Gender, age, marital status, education, occupation, economical level.	Screening
MINI	Psychiatric diagnosis	Screening
PHQ-9	Severity of depression	Screening, post-module, post-treatment and follow-ups
CSRI	Health and social services use	Screening and 12-month follow-up
BDI-II	Severity of depression	Baseline, post-treatment and follow-ups
SF-12	Health-related quality of life	Baseline, post-treatment and follow-ups
EQ-5D	Health-related quality of life	Baseline and follow-ups
PANAS	Positive and negative Affect	Baseline, post-modules and follow-ups
FFMQ	Facets and factors of mindfulness	Baseline and follow-ups
PHI	Remembered and experienced well-being	Baseline and follow-ups
ETS	Treatment expectations	Baseline
OTS	Treatment opinions	Post-treatment

*MINI* Mini-International Neuropsychiatric Interview, *PHQ-9* Patient Health Questionnaire-9, *CSRI* Client Service Receipt Inventory, *BDI-II* Beck Depression Inventory-II, *SF-12* Short Form-12 Health Survey, *EQ-5D* EuroQoL-5D Questionnaire, *PANAS* Positive and Negative Affect Scale, *FFMQ* Five Facet Mindfulness Questionnaire, *PHI* Pemberton Happiness Index, *ETS* Expectation of Treatment Scale, *OTS* Opinion of Treatment Scale.

^a^Waves: screening, baseline, post-treatment (6 weeks for the “face-to-face MBI + TAU” and “TAU alone” or 12 weeks after baseline for the “Internet-delivered MBI + TAU”), post-module (after each individual module for the “face-to-face MBI + TAU” and for the “Internet-delivered MBI + TAU”), follow-ups (both 6 and 12 month follow-up measurements)

#### Diagnosis interview

##### -Mini international neuropsychiatric interview V-5.0.0 (MINI)

The MINI V-5.0.0 interview is structured based on the psychiatric diagnoses of DSM-IV and ICD-10 [43, 44]. To administer it, clinicians only need a brief training and a short period of time that oscillates around 15 min. This interview has proven to be an accurate interview for use in multicenter clinical trials. The MINI interview will be used in the screening to determine whether a potential participant meets the inclusion criteria for Major Depression or Dysthymia. However, for cost reasons, the MINI interview will not be applied at post-treatment or follow-up. The MINI V-5.0.0 has been translated and validated in the Spanish language [31, 35].

#### Primary outcome

##### *-Beck Depression Inventory II (BDI-II)* [45]

The BDI-II total score, as a continuous variable, will be used as the primary outcome measure at post-test. It has been widely used in clinical research to assess changes in depression severity [20]. Additionally, the BDI-II has shown good sensitivity and specificity in detecting major depressive disorder in the Spanish-speaking population [46]. It is composed of 21 items about symptoms characterizing major depression. The BDI-II total score can be obtained by adding up the answers, from a minimum of 0 to a maximum of 63 points. The BDI-II Spanish version has shown high internal consistency in both general (α = 0.87) and clinical populations (α = .89) [47].

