### Sample size

The sample size estimation was based on testing whether the trend in the change is different between the intervention groups throughout the 4 time points. Firstly, we assumed that MBI groups would be able to present moderately high effects, compared to “TAU alone”, on the BDI-II at post-treatment. To operationalize this, we considered a standardized difference between arms on the main outcome of d = 0.7, which corresponds to the average effect observed in ten studies comparing MBIs with different wait-list conditions [36] and surpasses the 0.5 standard deviation criterion considered clinically relevant in previous studies [37, 38]. A preceding study by our research group with mild or moderate depressed patients in a similar Spanish PC setting found BDI-II means and standard deviations (SDs) of 22 and 5, respectively [20]. The inclusion criteria used in this study restricted the entry of mild or moderate depressed patients, thus reducing the SD compared to the general population and presenting a less skewed distribution of the data, as we predict will occur in the present study. The effect size referred to above corresponds to a difference of 3.5 points, which implies a reduction of slightly more than 15% in the BDI-II scale used. According to the GLIMMPSE v2.0.0 – time x group interaction in a general linear repeated measures (RM) design – and GPower v3.1.9.4 – ANOVA test for RM within-between interaction – statistical tools, considering the referred difference between the “face-to-face MBI + TAU” vs. “TAU alone” groups of depressed patients, which corresponds to a partial eta square value of roughly 0.09 and an effect size f of 0.31, with a common mean at baseline of 22, a mean at post-test of 16 and 19.5 respectively, and a mean at post-test of 17 for the “Internet delivered MBI + TAU” condition, and assuming a one point reduction in each group at each following time point, a baseline correlation of 0.6 and a decay rate of 0.35, assuming a common SD of 5, a 5% significance level, a statistical power of 80% using a 1:1:1 ratio, and an univariate approach to RM with Greenhouse-Geisser correction [39], we needed 33 subjects in each group. Because we expected a dropout rate of approximately 20% [40], we inflated the numbers to reach a total sample size of 120 patients, 40 per arm [41].

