### Main analysis

The efficacy of the “face-to-face MBI + TAU” group compared to the “TAU alone” group will be estimated based on the main BDI-II outcome, which will be considered a continuous variable. Multilevel mixed-effects models will be developed by means of a RM design on an intention-to-treat (ITT) basis, using the restricted maximum likelihood (REML) method, in order to produce unbiased estimates of variance/covariance parameters [54]. Non-standardized slopes and 95% confidence intervals (95% CI) will be calculated by adjusting those variables that show significant differences between groups at baseline. In order to study the specific trajectories of each group throughout the trial and determine whether possible differences between groups are consistent over time, the ‘group x time’ interactions will be calculated. Cohen’s d effect sizes will be calculated at each time point using the combined standard deviation at baseline [64]. Effect sizes are small when d ≤ 0.2; medium when d = 0.5; and large when d ≥ 0.8 [65].

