### Level of significance

An alpha level of 0.05 will be established using a two-tailed test. The probability values relative to the main analysis will be adjusted according to Benjamini-Hochberg’s correction for multiple comparisons, but the secondary and exploratory analyses will not be corrected.

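### The protocol does not fix one deciding primary test: its statements on visit, model term, baseline adjustment and multiplicity do not agree

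*Protocol article*

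**What the plan says.** Five places in the protocol article bear on the primary test.

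- **Primary outcome (BDI-II):** the total score, as a continuous variable, "will be used as the primary outcome measure at post-test". This is one visit.
- **Sample size:** the calculation is for "testing whether the trend in the change is different between the intervention groups throughout the 4 time points", run as a "time x group interaction in a general linear repeated measures (RM) design" with "an univariate approach to RM with Greenhouse-Geisser correction". Post-test means are given for all three arms. The same section states the effect as a two-arm difference at post-test: "we considered a standardized difference between arms on the main outcome of d = 0.7", and "The effect size referred to above corresponds to a difference of 3.5 points".
- **Main analysis:** face-to-face MBI + TAU against TAU alone, by a repeated-measures mixed model (ITT, REML). "Non-standardized slopes and 95% confidence intervals (95% CI) will be calculated by adjusting those variables" that differ significantly between groups at baseline. Group-by-time interactions are calculated to describe trajectories and to see whether differences are consistent over time. No term is named as the one that decides.
- **Abstract, Methods:** the mixed models are adjusted for baseline scores.
- **Level of significance:** "The probability values relative to the main analysis will be adjusted according to" Benjamini-Hochberg, and secondary and exploratory analyses are left uncorrected. The Secondary analysis section places Internet MBI versus TAU, and all secondary outcomes, among the secondary comparisons.

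**The concern.** A reader who wants to know which p value decides the trial gets different answers from different sections. The outcome section points to one visit. The sample size points to an interaction over four visits and three arms. The main analysis is a two-arm model with no deciding coefficient. The multiplicity rule presupposes several main p values, yet one outcome, one contrast and one visit leave a single p value with nothing to correct. The Background adds to this, because its main hypothesis covers both MBI formats against TAU, so the corrected family could be visits, arms or model terms.

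The covariate set is unsettled too. Under the abstract, baseline BDI-II is always in the model. Under the Main analysis section, it enters only if a baseline test happens to be significant.

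Two things are at stake. The first is a choice of test that remains open once data are seen. The second is efficiency, since the power that 33 patients per group buy depends on whether baseline BDI-II is a fixed covariate and on whether the correction applies.

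**Working it through.** **Inputs (Sample size section).** Means at baseline, post-test, 6 and 12 months, using the stated one-point fall per later visit: face-to-face 22/16/15/14, Internet 22/17/16/15, TAU 22/19.5/18.5/17.5. SD 5, base correlation 0.6, decay 0.35, two-sided 5%, 33 per group.

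**Assumptions not in the protocol.** The decay is read as a linear-exponent form: correlation = 0.6^(1 + 0.35 × (gap − smallest gap)/(largest gap − smallest gap)). Visits are placed at 0, 1.5, 6 and 12 months (1.5 months being the 6-week post-test in Table 1) or equally spaced.

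**1. The plan's own figure: three-arm group-by-time test, Greenhouse-Geisser.**
- From post-test on, arm deviations from the visit mean of 17.5 are −1.5, −0.5 and +2. Their squares sum to 2.25 + 0.25 + 4 = 6.5.
- The visit pattern (0, 1, 1, 1), centred, is (−0.75, 0.25, 0.25, 0.25), with sum of squares 0.75.
- Interaction sum of squares = 33 × 6.5 × 0.75 = 160.9.
- Real spacing: the six correlations average 0.550, so the error variance is 25 × (1 − 0.550) = 11.26. Epsilon is 0.986. Noncentrality = 160.9/11.26 × 0.986 = 14.1. Power is 80.7%.
- Equal spacing: average correlation 0.567, error variance 10.84, epsilon 0.980, noncentrality 14.5. Power is 82.3%.

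So 33 per group reproduces as a three-arm interaction. With the two main-contrast arms alone, the same test has 87-88% power and would need only 27-28 per group. The reproduction depends on the correlation form: ignoring the stated decay, constant correlation 0.6 gives 86% and a first-order autoregressive pattern gives 65%.

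**2. Two-arm difference at post-test, unadjusted.**
- n = 2 × (1.960 + 0.842)² × 5²/3.5² = 32.04, so 33 by the normal formula.
- Exact t at 33: noncentrality 0.7 × √(33/2) = 2.843, df 64. Power is 80.0% (81% by the normal approximation).

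**3. The same contrast with baseline BDI-II as covariate.**
- Residual SD = 5 × √(1 − 0.6²) = 4, so the standardized difference is 3.5/4 = 0.875.
- Noncentrality 0.875 × √(33/2) = 3.554, df 63. Power is 93.8%.

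**4. Post-test contrast after Benjamini-Hochberg, family assumed.**
- Three post-baseline visits, face-to-face versus TAU, t-tests without baseline adjustment, constant 3.5-point gap, 20,000 simulated trials: the post-test null is rejected in about 76-77% of trials, depending on visit spacing (76-78% as a rounded range).
- If the family were the two MBI-versus-TAU contrasts at post-test, about 75%.
- With baseline adjustment, even the strictest threshold for three tests (0.05/3) leaves 86%.

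| Reading, 33 per group | Power |
|---|---|
| Three-arm interaction | 81-82% |
| Two-arm interaction | 87-88% |
| Post-test, unadjusted | 80% |
| Post-test, Benjamini-Hochberg over three visits, unadjusted | 76-78% |
| Post-test, baseline-adjusted | 94% |

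**The case against.** The strongest defence is that the sections can be read together. The outcome section gives the visit, the Main analysis gives the arms and the model, and one repeated-measures model with visit as a category yields the post-test contrast. The group-by-time terms have a stated descriptive role. Benjamini-Hochberg adjusts p values and is not a rival test. The trend wording and the three-arm means in the Sample size section are one basis, not two. This is also a condensed article, and time coding or the correction family may be set out in an analysis plan that is not shown. All of this stands, and it is why the point is one of conflicting and unsettled statements, not of several incompatible tests.

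Three stronger readings are tempting and should not be drawn.

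- **That slopes and trend mean a linear slope over time, so that power is far below 80%.** No section makes time linear. A Greenhouse-Geisser correction belongs to a visit factor with several degrees of freedom, effect sizes are planned at each time point, and the assumed means drop sharply and then run parallel. Non-standardized slopes may simply mean unstandardized coefficients.
- **That Benjamini-Hochberg costs a great deal of power because the effect fades.** The plan assumes a constant 3.5-point gap.
- **That the 5% error rate is lost through a free choice of visit.** The protocol names a visit and says that main-analysis p values will be corrected.

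What the defence does not remove is that the favourable reading has to be assembled by the reader. The abstract and the Main analysis disagree on baseline adjustment, and a correction for several main p values does not fit a single main contrast.

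**Conclusion.** The point holds as a conflict in what the protocol states. It gives no single deciding test: the visit comes from one section, the powered hypothesis from another, the deciding model term from none, the baseline covariate differs between abstract and Main analysis, and the multiplicity rule has no identifiable family.

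The 80% power claim is not shown to be wrong. Under the natural reading with visit as a category, it is met or essentially met for the three-arm interaction and for the unadjusted post-test contrast. It slips modestly, to about 76-78%, only if the correction runs over three post-baseline visits and baseline is left out. Fixing baseline BDI-II as covariate takes the post-test contrast from 80% to about 94% at the same 33 per group.

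These figures rest on the plan's means, SD and correlation of 0.6. The interaction and Benjamini-Hochberg figures also rest on the assumed decay form and visit spacing, and the latter on the assumed family. The change should be made, but it is a matter of clarity and efficiency, not of an undersized trial.

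**What to change.** - **Primary outcome and Main analysis:** name one primary test, the face-to-face MBI + TAU versus TAU alone difference in BDI-II at post-treatment. Take it from the planned mixed model with visit as a categorical factor and baseline BDI-II as a prespecified covariate, two-sided 0.05. Table 1 puts this visit at 6 weeks in both arms. Make the abstract and the Main analysis agree on the covariate, so that it does not depend on a baseline significance test.
- **Later visits:** make the 6- and 12-month contrasts and the group-by-time trajectories secondary.
- **Level of significance:** drop Benjamini-Hochberg for this single test, or list the p values it covers.
- **Sample size:** restate the power for this two-arm contrast, keeping 40 per arm.

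The cost is wording in these sections and the abstract, with no extra patients or data. The one real loss is that the trajectory test gives up primary status. The article describes the study as still recruiting, so the change should be made and dated before outcomes are compared by arm.

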#### Secondary outcomes

##### -Sociodemographic variables

The sociodemographic variables that will be collected are the following: gender, age, marital status (single, married/relationship, separated/divorced, and widowed), education (no studies but can read and write, primary education, secondary education, University studies, and others), occupation (student, housework, unemployed, employee, sick leave, retired, disability, and other), and economic level (< 1 minimum inter-professional salary –MIS, 1-2 MIS, 2-4 MIS, and > 4 MIS).

##### *-The Patient Health Questionnaire 9 (PHQ-9)* [48]

This questionnaire is also one of the most widely used in research to evaluate depression severity. It is a brief instrument consisting of 9 items scored from 0 (“not at all”) to 3 (“nearly every day”), and it is completed by the patient. In this trial, the Spanish validated version will be used [35].

##### -Positive and negative affect scale (PANAS) [49]

This questionnaire is composed of 20 items and two independent dimensions: positive affect (PA) and negative effect (NA). Each scale has 10 items, and the score range for each is from 10 to 50. The psychometric properties of the PANAS are satisfactory. The Spanish version will be used [50].

##### *-The Pemberton Happiness Index (PHI)* [51]

The PHI is used to assess remembered well-being (general, hedonic, eudaimonic, and social well-being) through 11 items rated on a Likert scale ranging from 0 (strongly disagree) to 10 (strongly agree). In addition, experienced well-being (positive and negative emotional events that may have happened the day before) is also measured through 10 items answered dichotomously (yes or no). In this study, the Spanish validated version will be used [51].

### Other outcomes

#### Health-related quality of life

##### *-Sort Form-12 Health Survey* (SF-12) [52]

This instrument measures health-related quality of life and general functioning. The SF-12 consists of 12 items that have demonstrated adequate psychometric properties in its Spanish version [53, 54].

##### *-EuroQoL-5D* (EQ-5D) [55, 56]

The EQ-5D is an instrument commonly used to measure health-related quality of life. Participants self-report problems in the following five domains: mobility, self-care, usual activities, pain/discomfort, and anxiety/depression. Each one of them is divided into three severity levels corresponding to no problems, some problems, and extreme problems, which makes it possible to obtain a population-based score or societal index (SI). In addition, the participant will self-assess his/her current health status on a 10 cm vertical line where the best and worst imaginable health states score 100 and 0, respectively. The scores for these health-related states will be assigned using the readily available Spanish population rates [40, 41].

#### Cost-effectiveness

##### *-Client Service Receipt Inventory* (CSRI) [57]

This questionnaire is used to collect information about healthcare uses and social care services, in addition to other economic impacts (such as time off work due to illness). The variant used in this study was designed to collect retrospective data on service utilization during the 6 months prior to the assessment. The Spanish validated version will be used [58].

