## Methods

### Study design

Participants will be randomly allocated to a three-armed randomized controlled clinical trial with three conditions: a) “face-to-face MBI + TAU”, b) “Internet-delivered MBI + TAU”, and c) “TAU alone”. They will be assessed at pre- and post-treatment and 6- and 12-month follow-ups. The study flowchart is shown in Fig. 1. The study is currently in progress in the data recruitment stage.

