### Cost analysis

Cost will be calculated from healthcare and societal perspectives during the 12 months before the screening and during the 12 months before the last follow-up. The cost of pharmacological therapy, medical tests, and use of health services will be added together to calculate direct healthcare costs. Indirect costs such as loss of productivity will be calculated considering the minimum daily wage in Spain and the number of sickness absence days. Total costs will be estimated by adding up direct and indirect costs in €. The effectiveness of the interventions will be estimated as the difference between the BDI-II score at baseline and at follow-up, and utility will be estimated using quality-adjusted life-year (QALYs) at follow-up. QALYs will be calculated using the area-under-the-curve (AUC). Cost-effectiveness will be analyzed through the estimation of incremental cost-effectiveness ratios (ICERs). Cost-utility will be calculated through the estimation of incremental cost-utility ratios (ICURs). Cost-utility planes will be plotted.

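### As scheduled, the service-use questionnaire observes only 6 of the 12 months in each planned cost window, and none of the treatment period

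*Protocol article*

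**What the plan says.** The protocol article makes three statements that bear on the cost data.

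- **Recall period.** In the CSRI paragraph under Cost-effectiveness, the variant used is "designed to collect retrospective data on service utilization during the 6 months prior to the assessment".
- **Schedule.** In Table 1 (Instruments), the CSRI row reads "Screening and 12-month follow-up". Other rows say follow-ups in the plural, which the footnote defines as both the 6- and 12-month visits. The CSRI row names the 12-month visit alone. The same section says: "All variables and assessment periods of the study can be found in Table 1".
- **Cost windows.** Under Cost analysis, costs are to be calculated "during the 12 months before the screening and during the 12 months before the last follow-up".

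On components, Cost analysis says: "The cost of pharmacological therapy, medical tests, and use of health services will be added together to calculate direct healthcare costs". Indirect costs are to come from "the minimum daily wage in Spain and the number of sickness absence days". The CSRI paragraph says the form also records time off work. No record extraction or other source of resource use is mentioned.

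The same section defines effectiveness as the BDI-II difference between baseline and follow-up, and utility as QALYs by area under the curve. Table 1 places the EQ-5D at baseline and at both follow-ups.

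**The concern.** A form that looks back 6 months and is given twice, about a year apart, cannot fill two 12-month windows. In each window the earlier half has no stated data source. For the on-study window, the missing stretch is the one that includes or directly follows treatment.

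The stake is the economic evaluation. Comparing the cost-effectiveness of both formats with usual care is a stated aim at the end of the Background. There is also a directional hypothesis that both mindfulness arms will be more cost-effective than usual care, and the Discussion lists the cost-effectiveness comparison among the study's strengths. Service use that was not recorded cannot be recovered by the choice of analysis. The loss becomes harder to repair as each participant moves past month 6.

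**Working it through.** **Inputs**

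- Recall length: 6 months (CSRI paragraph).
- CSRI times: screening and 12-month follow-up (Table 1).
- Planned windows: 12 months before screening and 12 months before the last follow-up (Cost analysis).
- Post-treatment assessment: "6 weeks for the “face-to-face MBI + TAU” and “TAU alone” or 12 weeks after baseline for the “Internet-delivered MBI + TAU" (Table 1 footnote).
- Follow-up times: "They will be assessed at pre- and post-treatment and 6- and 12-month follow-ups" (Study design). The article does not say whether the 6 and 12 months run from baseline or from post-treatment, so both are tried.
- Assumption: screening and baseline are both treated as time 0, because the interval between them is not given.

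**Method.** Observed months are the overlap between the recall intervals, each running from (assessment − 6) to the assessment, and each planned window. The plan's own figure to be reproduced is 12 months in each window.

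**Pre-screening window**, −12 to 0. Recall covers −6 to 0, so 6 of 12 months are observed (6/12 = 50%).

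**Window before the last follow-up.** If the last visit is at month F, the window is F − 12 to F and recall covers F − 6 to F. Again 6 of 12 months are observed, whatever F is. The planned 12 months are therefore not reproduced in either window.

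**Where the on-study gap lies.** Weeks are converted at 12/52 month per week: 6 × 12/52 = 1.38 and 12 × 12/52 = 2.77 months.

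| Follow-ups counted from | Last visit F (months from baseline) | Unobserved stretch, 0 to F − 6 |
|---|---|---|
| Baseline | 12.00 | 0 to 6.00 |
| Post-treatment at 6 weeks | 13.38 | 0 to 7.38 |
| Post-treatment at 12 weeks | 14.77 | 0 to 8.77 |

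Treatment ends by 1.38 or 2.77 months, so it is unobserved in every row. In the last two rows it also precedes the 12-month window itself, which starts at F − 12 = 1.38 or 2.77 months. The gap then differs between the Internet arm and the other two.

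**Effect on the two ratios.** The ICUR divides a cost difference by a QALY difference, and the QALYs use EQ-5D from baseline through the 12-month visit. About 6 months of service use would be set against that whole period. The ICER divides the same partial cost difference by BDI-II change from baseline, and QALYs do not enter it.

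**Scaling up.** Take follow-ups from baseline, and let D1 and D2 be the between-arm cost differences in the first and second 6 months. The wanted numerator is D1 + D2. Doubling the observed half gives 2 × D2. The error is 2 × D2 − (D1 + D2) = D2 − D1, which is zero only if the arm difference is the same in both halves. The documents give no figure for D1 or D2, so neither its size nor its sign can be stated.

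**Does an added form close the gap?** With a 6-month-recall CSRI also at the 6-month follow-up, the window before the last visit is covered 12 of 12. The pre-screening window stays at 6 of 12. A 12-month recall at the two existing assessments would cover 12 of 12 in both windows. If follow-ups run from post-treatment, neither change reaches back to baseline.

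**The case against.** The best reply is that this is a condensed article. Cost analysis names no data source and does not say that the CSRI is the only one. Prescriptions, tests and sick leave could come from health-centre records. That limits the claim: the 12-month costs are not obtainable from the data collection described, but they are not impossible to obtain. It does not remove the conflict, because recall length, schedule and window length are each stated outright, and Table 1 is said to be complete.

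A reader might also infer four stronger things that the documents do not support.

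- *That half the costs are missing.* Half the months are unobserved. Nothing shows that costs are spread evenly over them.
- *That both ratios suffer from a mismatch with QALYs.* QALYs enter only the ICUR.
- *That the arms differ most in service use during treatment.* No figure supports this. The eligibility section also excludes from analysis cases with increased medication or another psychological treatment, which would restrict such differences. The objection to scaling up is only that equality of the two halves is unverified.
- *That the cost of delivering the mindfulness programme is left out, biasing the result in its favour.* The article does not say that it is excluded. Sessions may fall under use of health services, and such costing detail is commonly left to a fuller document.

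Finally, the primary outcome and main analysis rest on the BDI-II and do not use the CSRI. That stands, and it bears on how serious the point is.

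**Conclusion.** The point holds as an inconsistency between three explicit statements. The stated instrument and schedule observe 6 of the 12 months in each planned cost window and no part of the treatment period, and no other source is named to fill the gap.

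The 6-of-12 result does not depend on the follow-up anchor. The length of the on-study gap does: 6 months if follow-ups run from baseline, about 7.4 or 8.8 months, depending on the arm, if they run from post-treatment. The effect on either ratio cannot be quantified from the document.

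This should be fixed, because the planned economic analysis cannot be carried out from the data collection described. It is confined to that analysis.

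**What to change.** 1. **Schedule.** Add the CSRI at the existing 6-month follow-up in Table 1, and add the 6- and 12-month forms to obtain on-study cost.
2. **Pre-screening window.** Restate it in Cost analysis as 6 months, or use a 12-month recall at screening. With the first option, pre-study and on-study costs cover different lengths, so they should not be compared directly without saying so.
3. **Anchor.** State whether follow-ups run from baseline or from post-treatment. If from post-treatment, extend the recall of the first on-study form back to baseline and word the cost window to start there, so that the treatment period is costed in all arms.
4. **Participants already past month 6.** Use a longer recall at the last visit (12 months, or back to baseline if follow-ups run from post-treatment) or health-centre records, applied in the same way in all arms. The trial was registered in January 2017 and the article of October 2019 still describes recruitment as under way, so such participants are likely. For any who have completed the 12-month visit, records are the practical route.

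The cost is one more questionnaire at a visit that already takes place, short edits to Table 1 and Cost analysis, and some record work for earlier participants. The drawback is mixed recall lengths between earlier and later participants. These should be reported by arm, with a sensitivity analysis limited to participants who have both on-study forms.
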